### Comparison intervention

Patients allocated to the control group will receive AAU, which is the standard assessment that patients receive in the clinic, administered as follows: the patients are referred to the clinic by a family doctor or a private practice psychiatrist. On intake to the clinic, they will receive a diagnostic interview with either a medical doctor or a psychologist which can be supplemented with specific psychological tests, (e.g., SCID-5) when personality disorders are suspected, depending on the current resources and competencies in the clinics and following request from the head of treatment. Supplementary assessment is indicated roughly in one case out of ten. Otherwise, AAU patients are on the waitlist for the group therapy and are not followed by any therapist. Following the end of the MCA intervention, MCA patients might also wait a short while for group therapy, not seeing any psychotherapist in that interval. As all participants start group therapy, they will have a designated contact person, but only one preparatory individual therapy session before entering the specific treatment group.

### Intervention fidelity

The intervention will be carried out by the first author, a resident in psychiatry. He has received training and supervision on the assessment battery from national experts in the field. The intervention will be supervised by the third author, who is trained in therapeutic assessment. Audio or video recordings of MCA consultations will be used for supervision purposes and to secure intervention fidelity.

#### Outcomes’ objective 1: Feasibility

Acceptability: The feasibility criterion for acceptability in patients is supported if 25% of patients who are found eligible for inclusion and who have received formal information (information meeting with the first author) about the trial agree to participate in the trial.Satisfaction: The feasibility criterion for satisfaction in patients is supported if the mean CSQ-8 score is ≥ 3 (see below for description of instrument).Adherence: The feasibility criteria for adherence in patients is supported if 75% complete the MCA intervention (attend all MCA sessions including feedback-session).Time spent on the intervention: We evaluate the resources used to complete the study by recording the time spent in direct contact with the patient used to complete the MCA intervention [48].Evaluation of the Intervention Questionnaire (EQ)Adverse events

#### Outcomes’ objective 2: Trial outcomes

See Table 1 for a table of measurements.

**Table 1 Tab1:** Table of measurements CO-ASSM-RCT

	**Baseline (T0)**	**End of intervention (T1)**	**After 4 sessions of group psychotherapy (T2)**
URICA	x	x	
LSAS	x	x	x
RSES	x	x	x
GSES	x	x	x
CSQ-8 ^a^		x	x
PROM	x	x	x
EHR ^a^			x
EQ ^a^		x	
RPI	x	x	

^a^Feasibility outcomes

### Primary outcome

#### University of Rhode Island Change Assessment Scale (URICA)

URICA is a 32-item self-report measure including 4 subscales, designed to quantify the patient’s motivation for change: The four subscales are Pre-contemplation, Contemplation, Action, and Maintenance [60]. We will utilize the Contemplation score as our primary outcome.

### Secondary outcomes

#### The Liebowitz Social Anxiety Scale-Self-Report (LSAS)

The self-administered 24-item LSAS-SR [60], which is highly correlated with the clinician-administered version [61], includes questions pertaining to social interaction and performance situations. The LSAS-SR has shown to have good convergent, discriminant validity, and reliability [62].

### Rosenberg Self-Esteem Scale (RSES)

The RSES is a 10-item measure of self-esteem that includes five positive items and five negative items which are reverse-scored [63]. In general, the RSES has demonstrated good convergent validity and good test–retest reliability, and in similar populations of adults with social phobia, the RSES has demonstrated high internal consistency [64].

### General Self-Efficacy Scale (GSES)

The GSES is a 10-item psychometric scale that is designed to assess optimistic self-beliefs to cope with a variety of difficult demands in life. In contrast to other scales that were designed to assess optimism, this one explicitly refers to personal agency, i.e., the belief that one’s actions are responsible for successful outcomes [65, 66].

### Exploratory outcomes

#### Readiness for Psychotherapy Index

The RPI is a 42-item self-report measure that uses a 5-point Likert scale to assess 7 dimensions of readiness for psychotherapy: level of distress, desire for change, willingness to work in therapy, recognition of problems as psychological, willingness to discuss personal matters, willingness to endure discomfort in therapy, and responsibility for change [67]. The questionnaire will be translated and validated for use in a Danish mental health service population as part of the present study.

### National Patient-Reported Outcome Measures (PROM)-Psychiatry

The Danish National PROM is a 19-item self-report measure covering patients’ own views on their mental and physical health and level of general well-being [68]. It includes the WHO Well-Being Index (WHO-5), the Work and Social Adjustment Scale (WSAS) [69], and general items from the SF36.

### Data from Electronic Health Records (EHR)

We will monitor the number of no-shows and the number of diagnostic re-classifications by accessing the included patients’ EHR.

### User evaluations

#### Client Satisfaction Questionnaire (CSQ-8)

The CSQ-8 is a self-report questionnaire, constructed to measure satisfaction with services received by individuals and families [70].

### Evaluation of the Intervention Questionnaire (EQ)

This questionnaire focusing on the patient’s and therapist’s evaluation of the intervention, which is purpose-made for the current study, will be distributed at the end of the intervention. Items will be constructed as Likert Scale feedback forms consisting of a list of statements about different aspects of the course of the intervention. Response possibilities are five categories ranging from “very much in agreement” to “not at all.”

### Adverse effects

We expect no serious risks or adverse effects to the included patients. We monitor for adverse events, in particular suicidal behavior/ideation, and will check for this at every visit to the clinic. If a patient is admitted during participation in the study, a senior consultant (RB) will decide whether the patient can continue to participate.

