**Methods:**

We describe a randomized controlled feasibility and superiority trial of 42 individuals with a clinical diagnosis of either SP or AvPD, who are to initiate psychotherapeutic treatment in Danish outpatient mental health services. They will be randomized in a 1:1 ratio to either assessment-as-usual and receive no further assessment or to a Modified Collaborative Assessment (MCA) provided as a pre-treatment intervention before psychotherapy initiation. MCA will include a battery of psychological tests designed to thoroughly assess the patients’ psychopathology. The tests are administered in collaboration with the patient, including detailed oral and written feedback. We hypothesize that the intervention is feasible regarding patient’s acceptance and adherence. We further hypothesize that patients randomized to MCA will reach higher levels of readiness for psychotherapy as assessed with the University of Rhode Island Change Assessment Scale (URICA).

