## Discussion

The current study will be the first RCT investigating MCA in a mental health service setting. It will be a feasibility study and will test the study hypothesis in a small clinical sample. If the present study is successful, it may be followed up by other, larger clinical studies on MCA. The study will contribute to sparse existing research concerning the impact of clinical assessment; it will provide important new knowledge about the effects of routine and systematic patient-centered clinical assessment and generate effect size measures for future power calculations. It will also generate data regarding patients’ readiness for psychotherapy, and the percentage of patients who are wrongly diagnosed in a prototypical Danish public psychotherapeutic healthcare clinic.

We believe that the intervention will have a positive effect on the included patients. However, there is a risk that the patients receiving MCA may not benefit from the excess assessment but that the treatment will instead increase dropout due to the patient becoming overwhelmed. There is also a possibility of the patients becoming upset or disappointed due to the new knowledge they receive about themselves. Ultimately, the MCA may yield an unexpected diagnosis which could severely change the way the patient sees herself and the way society in general sees the patient. Many of these problems may, however, also occur in AAU. We will evaluate this by comparison of dropout from MCA and AAU.

If the current project documents the feasibility of the approach, further studies should examine the incremental value of MCA on patient outcome in terms of treatment completion or number of treatment sessions attended, and cost-effectiveness.

By the end of the present project, we will be able to decide whether the results are sufficiently promising to pursue a full trial (phase III) [73]. For that purpose, the study output also encompasses the development of a MCA protocol for clinicians and an adjoining fidelity instrument.

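### Between T0 and T1 the described adverse-event check relies on visits that most AAU patients do not have, and dropout has no defined AAU counterpart, so the harm comparison is not like-for-like

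*Protocol article*

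**What the plan says.** The abstract's Discussion paragraph lists safety among the things assessed, and the feasibility outcomes (objective 1) include adverse events. Under Adverse effects, the article says that events are monitored, "in particular suicidal behavior/ideation, and will check for this at every visit to the clinic". It also mentions hospital admission, but only as the trigger for a decision on continued participation.

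Contact before T1 differs by arm. MCA adherence means attending every session, including the feedback session; the number of sessions is not given. The abstract says that control patients get "assessment-as-usual and receive no further assessment". Under Comparison intervention, "AAU patients are on the waitlist for the group therapy and are not followed by any therapist", with one exception: "Supplementary assessment is indicated roughly in one case out of ten". After that the arms converge: "As all participants start group therapy, they will have a designated contact person, but only one preparatory individual therapy session".

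Table 1 contains no adverse-event item at T0, T1 or T2. Health records are to supply no-shows and diagnostic re-classifications, and Table 1 places them at T2.

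The Discussion raises three possible harms of MCA: being overwhelmed and leaving, being upset or disappointed, and receiving an unexpected diagnosis. It then states: "We will evaluate this by comparison of dropout from MCA and AAU".

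**The concern.** A check tied to visits finds more events where there are more visits. In the interval in which MCA is delivered, one arm is seen repeatedly and the other is mostly not seen. A difference in recorded events could then reflect only how often patients were asked.

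The dropout comparison has a related problem. Leaving a multi-session intervention is an observable event with a definition. Leaving a waiting list has none in the article. Dropout is also a weak measure of distress or of the effect of a new diagnosis, which are two of the three harms it is meant to cover.

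The trial is to inform whether a full-scale study is pursued. A harm comparison that favours either arm for reasons of measurement could mislead that decision.

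**Working it through.** **Plan's own figure.** The article gives no event rate, visit count or expected dropout difference for the safety comparison, so there is no figure to reproduce. Its sample-size calculation concerns the readiness score and does not bear on this point. From it I use only 42 patients allocated 1:1, so 42/2 = 21 per arm.

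**Step 1: planned opportunities to detect an event**

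| Window | MCA | AAU |
|---|---|---|
| T0 to T1 | Several sessions, including feedback | No planned contact, except supplementary assessment in about 1 in 10 |
| Preparatory session to T2 | One preparatory session, then group therapy | Same |

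The imbalance is confined to the first window. There it affects about 0.9 × 21 = 18.9, or roughly 19 of 21 AAU patients. This counts the one-in-ten supplementary assessments as falling after randomisation, which is generous to AAU because the article describes them as part of intake.

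**Step 2: illustration of the size.** All inputs except the 21 per arm and the one in ten are assumptions:
- the same true risk r of an event between T0 and T1 in both arms, 10% or 20%;
- probability q that a visit detects an existing event, 50% or 90%, independent across visits;
- k MCA visits, 3 or 6, all able to detect the event;
- one visit for 10% of AAU patients.

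Expected detected events: MCA = 21 × r × [1 − (1 − q)^k]; AAU = 21 × r × 0.1 × q.

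| r | q | k | MCA | AAU | Ratio |
|---|---|---|---|---|---|
| 0.10 | 0.5 | 3 | 1.84 | 0.11 | 17.5 |
| 0.10 | 0.5 | 6 | 2.07 | 0.11 | 19.7 |
| 0.10 | 0.9 | 3 or 6 | 2.10 | 0.19 | 11.1 |
| 0.20 | 0.5 | 3 | 3.68 | 0.21 | 17.5 |
| 0.20 | 0.5 | 6 | 4.13 | 0.21 | 19.7 |
| 0.20 | 0.9 | 3 or 6 | 4.20 | 0.38 | 11.1 |

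First row worked: 21 × 0.10 × (1 − 0.5³) = 21 × 0.0875 = 1.84; 21 × 0.10 × 0.1 × 0.5 = 0.105; ratio 17.5. The risk r cancels from the ratio, which is driven mainly by the one-in-ten figure. Events that come to light later, for example at the preparatory session, would narrow the gap.

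**Step 3: dropout.** The adherence criterion is met at 75% MCA completion, so up to 0.25 × 21 = 5.25, or 5 patients, could fail to complete with the criterion still satisfied. No AAU number can be set beside this. The objectives mention adherence to AAU, but the article does not say what non-adherence to AAU would be.

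**The case against.** The strongest reply is that the article describes less imbalance than one might infer. Several stronger readings are tempting and are not supported.

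- *AAU patients have no visits.* This is true only before T1, and then for about nine in ten. All participants are later due a preparatory session and group therapy, where the visit-based check applies equally.
- *Events are sought only at visits.* The article does not say only. Admissions can come to notice without a study visit, and a fuller protocol may describe other collection. What stands is that no other active check is described, and that neither the table of measurements nor the planned use of health records covers adverse events.
- *AAU dropout is zero by construction.* It is not. AAU patients can withdraw, leave the waiting list, miss T1 or not start group therapy, and the allowance of about 15% attrition covers the whole sample. The Discussion does not equate dropout with missed MCA sessions. What stands is that the term has no common definition.
- *Deterioration on the waiting list goes unseen.* Symptoms and well-being are self-reported online at T0, T1 and T2 in both arms (LSAS, PROM). Discrete events such as suicidal behaviour are what could be missed.

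It is also fair to say that no formal between-arm test of adverse events is planned, that counts from about 21 per arm are descriptive under any method, and that adherence to group therapy in the first four weeks is already compared between arms. These points limit the consequences. They do not make the T0–T1 counts or the stated dropout comparison like-for-like.

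**Conclusion.** The concern holds for the window from T0 to T1 and for the dropout comparison. On the procedures described, adverse events before T1 would be ascertained unequally, probably producing an apparent excess in MCA. The dropout comparison sets a defined quantity against an undefined one.

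The size cannot be derived from the article. Under the stated assumptions, equal true risks would show as an 11- to 20-fold excess of detected events, but in absolute terms that is only about two to four events against fewer than one. It illustrates direction and order and does not predict results. A reader should not conclude that the whole safety assessment is uninformative: the period from the preparatory session to T2 is balanced in planned contact, and the self-report scales do not depend on visits. The primary outcome is not affected.

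**What to change.** 1. Base the between-arm safety comparison on events counted over identical windows from randomisation, by a method that does not depend on visits. Extend the health-record review to adverse events and admissions in both arms. Where collection is still open, add an identical adverse-event item to the T1 and T2 questionnaires.
2. List events elicited at MCA visits separately and keep them out of the between-arm comparison.
3. Define dropout identically in both arms from randomisation: trial withdrawal, not starting or stopping group therapy, and non-response at T1 or T2. Report non-completion of MCA sessions separately, as adherence.

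The cost is a wider extraction from records already being accessed and, if feasible, one questionnaire item. The Trial status section says that the intervention ran to April 2023, so a new T1 item can probably no longer reach participants. The record review and the common definition can still be fixed in the statistical analysis plan, which the article promises before data processing starts. Events never entered in the health record may still be missed, and the report should say so.

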### Patient and public involvement

We will establish a user panel who will help interpret the findings of the study, and we will include the feedback in our reporting of the findings of the present study, and in the preparations for a possible full-scale phase-3 study of the intervention. The user panel will include five patients recruited from the clinics and they will meet two times throughout the study. They will be users of the Danish MHS but not participants in this trial.

#### Statistical considerations

As the primary objective of the present trial is to test feasibility, a formal power calculation is not required. However, the present trial also wishes to examine MCA versus AAU, and we present the following power calculation for the primary outcome: readiness for change. Sample size calculation is based on figures in Dozois et al. [71] of patients with panic/anxiety, where the primary outcome “Contemplation stage score” in readiness for change was mean 37.3 (SD 1.9) for CBT responders and mean 34.4 (std 3.4) for non-responders, i.e., with significance level 5% and power 90%. This yields a total sample of 36 with 18 patients in each arm. We strive for 42 patients to account for attrition around 15%. We find it feasible to include the 42 patients since 64 patients are offered treatment packages annually (40 SP and 24 AvPD).

A detailed statistical analysis plan will be published on ClinicalTrials.gov prior to data processing initiation. Briefly, we expect to report descriptive data such as data for the feasibility criterion as percentages, means, and variation as standard deviation. Outcomes will be analyzed as continuous and categorical measures (i.e., responder status and new diagnosis, see below). All statistical analyses will be performed as intention-to-treat analyses (ITT); however, main outcomes will also be analyzed for completers only for sensitivity reasons. Missing data will be handled by the use of multiple imputations. The pre- to post-treatment effects of the MCU or AAU will be determined utilizing a series of repeated measures analyses of variance (rmANOVAs). Analysis will be based on masked data (recoded data for concealment of allocation). Conclusions of the main outcomes will be formulated prior to unmasking the data. Statistical calculations will be performed prior to unblinding. All statistical calculations will be performed in R and RStudio [72].

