### Objectives

The study objectives are to (1) explore the feasibility of MCA as an intervention through rates of recruitment of screened patients, patience’s adherence to MCA or Assessment As Usual (AAU), patient satisfaction ratings, and patient and therapist/clinician evaluations; (2) compare the effect of MCA versus AAU on levels of readiness for psychotherapy in patients referred to group therapy for social phobia or AvPD at end-of-intervention (T1) (main outcome) and after 1-month follow-up (T2); (3) compare the effect of MCA vs AAU on diagnoses (number of diagnostic revisions) and treatment offered (number of patients offered other or additional treatment) in patients referred to group therapy for social phobia or AvPD, as well as adherence to group therapy within the first 4 weeks; and (4) develop a fidelity checklist for the MCA intervention.

We hypothesize that MCA is feasible regarding acceptance and adherence in patients with social phobia or AvPD and is superior to AAU in increasing contemplation score (URICA, see below) at the end of intervention (T1). (2) In addition to this, patients offered MCA have higher service satisfaction ratings (CSQ) than those offered AAU prior to psychotherapy onset, and user evaluation scores of MCA (purpose-made) are positive (more than 3 on a 1–5 Likert Scale).

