## Methods

### Design

The present protocol is based on reporting guidelines from the SPIRIT guideline for Standard Protocol Items for Clinical Trials [45] adapted as recommended when reporting protocols of feasibility trials [46]. The study is designed in order to inform and evaluate the feasibility of a possible future, full-scale RCT of MCA versus AAU. We will evaluate the feasibility of the interventions in terms of clinician resources and patient’s acceptability and adherence to the intervention and comparator, selected based on recommendations for the conduct of feasibility trials [47–49].

In addition to these feasibility outcomes, we will assess outcomes regarding readiness for change, symptoms, and regarding self-esteem and self-efficacy. Data are gathered from patients through a number of questionnaires delivered by the RedCap © webmodule prior to randomization (T0), at the end of MCA (T1) and after 4 weeks of psychotherapy (T2)—the absolute time depends on clinical logistics and timing of group therapy onset.

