### Trial design

A two-armed, parallel randomized controlled feasibility and superiority trial comparing the effect of pre-treatment MCA with AAU.

A CONSORT diagram is provided in Fig. 1. A diagram of the proposed study and the outcome assessment is provided in Fig. 2. The trial data collection and randomization, stratified by gender, will be carried out in the web-based data management system REDCap (https://www.project-redcap.org/). Self-ratings will also be collected on the web-based REDCap platform.

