### Randomization and blinding

Patients will be randomized 1:1 to either the MCA or AAU on an individual level. Allocation to experimental intervention or comparison intervention will be computer-generated using the software REDCap © [50].

Due to the nature of the intervention, neither participants nor the researcher who will administer the intervention can be blinded to allocation. However, data will be re-coded for concealment and analyzed without access to information about allocation. The conclusion will be written prior to unblinding.

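### The primary URICA comparison is planned as a pre-post repeated-measures ANOVA with its between-arm test unnamed; ANCOVA on the T0 score already collected would be more precise at any plausible correlation

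*Protocol article*

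**What the plan says.** The Objectives section of the protocol article puts the primary efficacy hypothesis as a comparison of arms: MCA "is superior to AAU in increasing contemplation score (URICA, see below) at the end of intervention (T1"). The URICA section fixes the endpoint: "We will utilize the Contemplation score as our primary outcome". The Design section times the questionnaires "prior to randomization (T0), at the end of MCA (T1) and after 4 weeks of psychotherapy (T2"), but Table 1 marks URICA at T0 and T1 only.

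Statistical considerations then names the analysis. Its subject is "The pre- to post-treatment effects of the MCU or AAU" (MCU presumably stands for MCA), and these effects "will be determined utilizing a series of repeated measures analyses of variance (rmANOVAs"). The sentence does not name the term that carries the treatment comparison and mentions no baseline adjustment. The same section says that missing data will be multiply imputed and that a detailed statistical analysis plan will follow before data processing starts.

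The sample size in that section uses Contemplation means of 37.3 (SD 1.9) and 34.4 (SD 3.4) at a 5% level and 90% power. It arrives at 18 per arm, raised from 36 to 42 in total for attrition. Allocation is 1:1, and Trial design adds that "The trial data collection and randomization, stratified by gender, will be carried out" in REDCap.

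**The concern.** The hypothesis is about the difference between arms at T1, while the analysis sentence describes change from before to after treatment. A repeated-measures ANOVA with two arms and two visits offers three terms: arm, time, and arm by time. Only arm by time answers the stated question with full weight on the T1 effect. With two visits, that term is exactly the two-sample t-test on change scores.

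The change score fixes the slope on baseline at one. ANCOVA estimates the slope from the data and so removes more noise unless the two measurements are almost perfectly correlated. About 36 evaluable patients are expected, and the Discussion wants the trial to supply effect sizes for later power calculations. A noisier estimate therefore harms both the superiority test and that later use. A second issue is consistency: the sample size was derived for a comparison of single scores, which is not the test then planned.

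**Working it through.** **Inputs.** Difference 37.3 − 34.4 = 2.9; SDs 1.9 and 3.4; 18 per arm; 5% level, taken as two-sided because the article does not say; power 90%. All come from Statistical considerations. The T0–T1 correlation ρ is not given, so 0.3, 0.5 and 0.7 are assumed. The SD is taken as equal at both visits.

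**1. The plan's own figure.** For two means, n per arm = 2(1.960 + 1.282)² SD² / 2.9², where (1.960 + 1.282)² ≈ 10.51.
- Simple average SD, (1.9 + 3.4)/2 = 2.65: n = 17.5, so 18 per arm and 36 in total, as stated.
- Root-mean-square SD, √[(1.9² + 3.4²)/2] = 2.754: n = 18.95, so 19 per arm. With the t distribution, 18 per arm gives 86.6% power.
- Attrition: 36 × 1.15 = 41.4, which rounds up to 42; 36/0.85 = 42.4 would give 43.

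The 36 is therefore an unadjusted two-sample comparison of single scores, with no pre-post correlation in it.

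**2. Variance of the three candidate estimates**, relative to the unadjusted T1 difference:
- unadjusted T1: 1
- arm by time (change score): 2(1 − ρ)
- ANCOVA on T0: 1 − ρ²

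ANCOVA relative to change score is (1 − ρ²)/[2(1 − ρ)] = (1 + ρ)/2. At 36 patients, estimating the slope costs a factor of about 1 + 1/(36 − 4) = 33/32. The two methods break even where (1 + ρ)/2 × 33/32 = 1, which gives ρ = 0.94. The change score matches the unadjusted T1 comparison where 2(1 − ρ) = 1, which gives ρ = 0.5; below that it is worse.

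**3. Results** (difference 2.9, SD 2.754; n per arm for 90% power by the normal formula, without the slope penalty; power at 18 per arm by noncentral t and simulation):

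| ρ (assumed) | n per arm, change score / ANCOVA | ANCOVA/change variance ratio at 36 patients | Power, change score | Power, ANCOVA |
|---|---|---|---|---|
| 0.3 | 27 / 18 | about 0.66 | 74% | 89% |
| 0.5 | 19 / 15 | about 0.77 | 87% | 93–94% |
| 0.7 | 12 / 10 | about 0.88 | 98% | 99% |

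Example for ρ = 0.3: the change-score factor is 2 × 0.7 = 1.4, and 18.95 × 1.4 = 26.5, so 27 per arm; the ANCOVA factor is 1 − 0.09 = 0.91, and 18.95 × 0.91 = 17.2, so 18. In simulation the variance ratio was 0.98 at ρ = 0.9 and 1.01 at ρ = 0.95, which agrees with the break-even point.

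**4. Adding gender.** I simulated a gender term balanced across arms and with no effect on the score, using ordinary standard errors (18 per arm, 20,000 runs). Power was 88%, 94% and 99% at ρ = 0.3, 0.5 and 0.7. The extra covariate costs practically nothing even if gender is not prognostic.

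**The case against.** The strongest reply is that nothing here is an error. In a randomised trial the arm-by-time term is an unbiased test of a superior increase, which is how the hypothesis is worded. The article elsewhere says plainly that MCA is to be compared with AAU. Feasibility is the primary objective, and the analysis paragraph is introduced as a short summary ahead of a full plan. All of that stands. A reader might infer that the planned method does not test the hypothesis, or that the arm main effect is the intended test. That main effect would average in the T0 score, with power of only about 38–48% over ρ = 0.7 to 0.3. The text supports neither reading; it only leaves the term unnamed.

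Three other stronger readings also fail.
- That the plan ignores the gender stratum: the article does not say that gender is left out, and model covariates are commonly set in the analysis plan, which is announced and not shown. A stable gender effect on level would in any case cancel from a change score.
- That ANCOVA is always more precise: this is a large-sample result. At 36 patients the advantage ends near ρ = 0.94, with a loss of 1–2% beyond about 0.95.
- That the unequal SDs call for heteroscedasticity-robust (HC3) errors: 1.9 and 3.4 belong to responders and non-responders in an external study, not to the arms. With T0, gender and HC3 errors, simulated power was 86%, 92% and 98%, so about a third to all of the gain is given back.

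The reply does not remove the main point. The article positively chooses a method, so the choice is not a detail left open, and a better one is available on data already collected.

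**Conclusion.** The point holds as one of efficiency, of an unnamed contrast, and of a mismatch between sample size and analysis; it is not one of bias or invalidity. On the plan's inputs, replacing the arm-by-time test by ANCOVA on T0 Contemplation raises power by about 15 percentage points at ρ = 0.3, about 7 at 0.5 and about 1 at 0.7. The size rests wholly on ρ, which the article does not give, and on equal SDs at the two visits. The direction holds for any ρ below about 0.94, and a higher value is implausible for a self-report score taken before and after an intervention meant to change it. If ρ is below 0.5, the planned test is less precise than the comparison that justified 36 patients. The change should be made, but the trial is not invalid without it.

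**What to change.** In the analysis plan, before data processing starts:

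- Define the primary efficacy estimate as the between-arm difference in T1 Contemplation score, from an ANCOVA with arm, T0 Contemplation and gender (the randomisation stratum). Fit it in each imputed data set, pool the results, and report the adjusted difference with a 95% confidence interval. Use ordinary model-based standard errors.
- For LSAS, RSES and GSES, which Table 1 schedules at T0, T1 and T2, use the baseline-adjusted analogue for repeated measures, with the between-arm contrasts at T1 and T2 named.

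The cost is one or two degrees of freedom and a few sentences. No new data, visits or patients are needed.
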